### Sample size

On the basis of the data from the pilot study, carried out between June 2008 and January 2009 at the Kneipp Clinic in Bad Wörishofen, Germany, on 30 patients with pre-existing osteoarthritis of the hip or knee, a sample size was estimated using G-Power 3.0.10 software (Faul F, Erdfelder E, Lang A.-G, and Buchner A, 2007). According to this calculation, a sample size of n = 180 patients will suffice to determine a possible interaction between the groups with respect to the primary outcome, with a statistical power of 95%.

### Interventions

The study will divided into a **clinical or treatment phase **(two weeks' inpatient therapy) and a **follow-up phase **of a further ten weeks, ending with a telephone interview to be carried out by the external evaluation centre (Figure 2).

**Figure 2 F2:**
[figure not shown]
**Flowchart describing the participant flow through the study**. Diagramm over the participant flow through recruitment, randomization, baseline measurement, post-treatment and 3 month follow-up.

During the clinical phase the following interventions will be applied:

In **intervention group 1**, the patient will receive hydrotherapy appropriate for osteoarthritis of the hip or knee, in the form of daily thigh affusions of alternate cold and warm water. In this group, physiotherapy may also be given but not specifically for the affected hip or knee joint.

In **intervention group 2**, patients with osteoarthritis of the hip or knee will receive specific physiotherapy of the affected hip or knee joint three times a week, but **without **any disease-specific hydrotherapy. Because of the holistic approach of the clinic, however, these patients will still receive hydrotherapy at sites other than the affected joint, for example, alternate cold and warm affusions of the back or an ascending lumbar affusion.

In **group 3, the control group**, patients with active osteoarthritis of the hip or knee will receive specific, joint-related hydrotherapy in the form of a (daily) alternate cold and warm thigh affusions **as well as **joint-specific physiotherapy (three times a week).

### Diagnostic and biometric evaluation procedure

Each patient will undergo a medical examination at the time of admission and a final examination after two weeks of inpatient therapy, in which the general physical state and disease-specific previous medication and therapy will be documented. At the two medical examinations, pain intensity will be measured on a ten-point visual analogue scale, and 1) diagnostic assessment of the affected joint according to the neutral-zero method (hip joint: flexion and extension, internal and external rotation; knee joint: flexion and extension); 2) the timed "up and go" (TUG test) as an indirect assessment criterion of flexion and extension in the affected hip or knee joint; and 3) the body mass index (BMI) will be recorded in the case report form or physician's questionnaire.

**Independently of the doctor**, a standardised questionnaire will be filled out by the patient at the time of admission and after two weeks of inpatient therapy. These questionnaires will be sent to the evaluation centre directly after they are handed in.

The same assessment will be carried out in a telephone interview by the external study centre, ten weeks after the end of inpatient care.

The assessment includes A) the SF-36 test, B) the Lequesne hip or knee questionnaire, C) the AIM-2-SF Scales 2 Short Form, and D) the EQ-5D test.

In addition, each patient will be given a diary for self-reporting during inpatient treatment. This diary will be completed by the patient: it contains the subjective visual analogue scale, the current mental health state scale of the EQ-5 D test, and blood pressure measurements (filled out by the nursing staff) ((Figure 3)).

**Figure 3 F3:**
[figure not shown]
**Schedule of data acquisition**. [pq = physicians questionnaire]. EQ-5D = EuroQol questionnaire; AIMS2-SF = Arthritis Impact Measurement Scale.

### Outcome measures

#### Primary outcome measure

The primary outcome measure will be the pain intensity of the affected joint during inpatient care, as assessed by the patient and the investigator. The patient rates subjective pain intensity in the patient diary on a ten-point visual analogue scale (0 = no pain; 10 = greatest pain imaginable); the doctor also records pain intensity around the affected joint on a ten-point visual analogue scale. The use, practicality, and validity of visual analogue scales have been sufficiently evaluated and are scientifically accepted [30,31]

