**Methods/design:**

The study design consists of a prospective randomised controlled three-armed clinical trial, which will be carried out at a specialist clinic for integrative medicine, to investigate the clinical effects of hydrotherapy on osteoarthritis of the knee or hip joint, in comparison with conventional physiotherapy.

One hundred and eighty patients diagnosed with osteoarthritis of hip or knee will be randomly assigned to one of three intervention groups: hydrotherapy, physiotherapy, and both physiotherapy and hydrotherapy of the affected joint. In the first group, patients will receive Kneipp hydrotherapy daily, with water applied in the form of alternate cold and warm thigh affusions (alternating cold and warm water stimulation is particularly relevant to the knee and hip regions).

Patients in the second group will receive physiotherapy of the hip or knee joint three times a week. Patients in the physiotherapy-hydrotherapy combination group will receive both joint-specific physiotherapy three times a week and alternate cold and warm thigh affusions every day. Follow-up assessments will be on three levels: clinical assessment by the investigator; subjective patient assessment consisting of a patient diary, and questionnaires on admission and at the end of the treatment phase; and a final telephone assessment by the external evaluation centre. Assessments will be made at baseline, after two weeks of inpatient treatment, and finally after a further ten weeks of follow-up. The primary outcome measure will be pain intensity of the affected joint in the course of inpatient treatment, judged by the patient and the investigator. Secondary outcomes include health-related quality of life and joint-specific pain and mobility in the course of the study. Statistical analysis of the results will be on an intention-to-treat basis.

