## Methods/design

### Research aims and questions

The main aim of this three-armed clinical study will be to determine the effects of hydrotherapy with alternate cold and warm affusions of the thigh in the concomitant treatment of osteoarthritis of the hip or knee. The main outcome measures are pain reduction, improvement in the quality of life, and increased movement in the affected joint.

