### Randomisation and treatment allocation

Based on the results of a pilot study, a randomisation number list and treatment group assignment has been generated by software before the beginning of the main study. When the envelope is opened, the investigator and patient will come to know the treatment group assignment (group 1, 2, or 3) with a corresponding treatment plan in line with the study protocol, the patient diary for the inpatient treatment phase, and all the necessary assessment forms for both doctor and patient.

Prior to the study, all medical specialists in the clinic and attending therapists have been given a briefing on the study protocol, the ethical basis of this clinical study, the randomisation procedure, and the specific therapy for each treatment group, in line with the study protocol.

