#### III) Joint-specific pain and function rating on the basis of the Lequesne index

The Lequesne index is a patient-centred assessment (self-rating procedure) in the form of a questionnaire. It is available in two closely related versions (hip or knee joint diseases), and includes pain, walking performance, and coping with daily living. The evaluation shows high reliability, validity, and sensitivity to change.

As a self-rating procedure, the Lequesne index is not subject to the influence of the investigator or therapist. There is no investigator bias, which always has to be recognised within procedures combining self-rating and rating by another person. The Lequesne index is therefore a suitable assessment tool for quality assurance [33,34]. The patient will document this index for the affected joint at the beginning and end of the inhouse treatment period, and it will again be recorded by the external evaluation centre on the basis of the telephone interview at the end of the ten-week follow-up.

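### The primary outcome is two pain ratings, one by the unblinded investigator, with no printed rule for which decides, and the aims section names three main outcomes against this single primary

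*Protocol article*

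**What the plan says.** Under *Primary outcome measure* the Protocol article states: "The primary outcome measure will be the pain intensity of the affected joint during inpatient care, as assessed by the patient and the investigator". The abstract says the same: pain is "judged by the patient and the investigator". Two records follow. The first is the diary: "The patient rates subjective pain intensity in the patient diary on a ten-point visual analogue scale". The second is medical: "the doctor also records pain intensity around the affected joint on a ten-point visual analogue scale". *Diagnostic and biometric evaluation procedure* ties the medical record to admission and the end of the second week: "At the two medical examinations, pain intensity will be measured on a ten-point visual analogue scale". The diary is kept during the inpatient stay. The text at hand does not say how often its pain scale is completed.

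*Sample size* (180 patients, 95% power) and *Statistical analysis* (repeated-measures ANOVA of the VAS) both refer to the primary outcome in the singular, and neither names a rater.

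On knowledge of treatment, *Randomisation and treatment allocation* says: "When the envelope is opened, the investigator and patient will come to know the treatment group assignment".

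On the ranking of outcomes, *Research aims and questions* says: "The main outcome measures are pain reduction, improvement in the quality of life, and increased movement in the affected joint".

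**The concern.** Two people scoring pain on two records produce two variables. They have different raters and, as far as the text shows, different schedules. An analysis of the VAS cannot be run until someone decides which record it means. If that choice is made after the data are seen, a positive primary result will not be credible. If the ratings point in different directions, there is no agreed answer.

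One of the two ratings also has a specific weakness. Pain is a subjective symptom, and the investigator rates another person's pain while knowing which treatment that person received. Any expectation about hydrotherapy can enter the score directly.

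The aims section adds a second ambiguity, because it gives quality of life and movement the same rank as pain.

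**Working it through.** **Step 1. Set the passages side by side.**

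| Place in the Protocol article | What it implies |
|---|---|
| Abstract; *Primary outcome measure* | Primary is pain, two raters |
| *Diagnostic and biometric evaluation procedure* | Medical VAS at two examinations; diary VAS during the stay |
| *Sample size* | One primary outcome |
| *Statistical analysis* | One primary VAS, rater not named |
| *Randomisation and treatment allocation* | Investigator and patient both know the arm |
| *Research aims and questions* | Three main outcomes: pain, quality of life, movement |
| Abstract; *Research questions*, no. 3; *Secondary outcome measures* II and IV | Quality of life is secondary |
| Abstract; *Secondary outcome measures* I | Mobility is secondary |

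The first two rows do not fit the next two. The aims row does not fit the last two.

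**Step 2. The plan's own figure.** The 180 patients cannot be reproduced, because alpha, effect size, correlation and number of measurements are not printed. The figure is neither confirmed nor refuted here. For Step 5 I solved backwards for the effect size that gives 95% power.

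**Step 3. If either rating could count.** Assume alpha = 0.05 for each rating. With independent ratings:

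1 − (1 − 0.05)² = 1 − 0.9025 = 0.0975, or 9.75%.

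With correlated ratings, I simulated pairs of 2-degree-of-freedom tests (the large-sample form of a three-arm comparison of change), with 1,000,000 draws per setting:

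| Correlation of the ratings | Chance of at least one false positive |
|---|---|
| 0 (exact) | 9.75% |
| 0.3 | 9.5% |
| 0.5 | 9.2% |
| 0.7 | 8.4% |
| 0.9 | 7.1% |

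The documents give no correlation, so this is a range and not an estimate.

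**Step 4. If both ratings must succeed.** The chance that both are falsely positive cannot exceed the chance for one, so it stays at or below 5% and no split of alpha is needed. The price is power. If each rating had 95% power, the chance that both succeed could be as low as 1 − 2 × 0.05 = 0.90.

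**Step 5. If both were kept as alternatives with alpha split.** Each rating is tested at 0.05 / 2 = 0.025. For the group-by-time interaction with k = 3 groups, m measurements and correlation ρ between them:

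λ = f² × N × m / (1 − ρ), with df1 = (k − 1)(m − 1) and df2 = (N − k)(m − 1).

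For example, with m = 2, ρ = 0.5 and N = 180, 95% power at alpha 0.05 requires f = 0.1477. Then λ = 0.1477² × 180 × 2 / 0.5 = 15.7, with df 2 and 177. At alpha 0.025 the same f gives 91.3% power. For m = 2, 3 or 14, power per rating is 91.3% to 91.4%, and restoring 95% would take 210, 207 or 204 patients.

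**Step 6. With one rating named.** There is one test at one level. Nothing in this change alters N.

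**The case against.** The strongest reply is that this is a condensed article and the decision rule may stand in an analysis plan that is not shown. The printed wording joins the raters with *and*, which fits a rule that both must succeed, and under that rule there is no inflation. It could also be said that the doctor merely writes down the patient's answer. The possible rule elsewhere and the conditional nature of the inflation both stand. The core does not fall. The article does define its primary outcome, defines it as two assessments, and then sizes and analyses one. If the doctor only transcribes, there are still two records and no statement of which one counts.

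A reader might go further in four ways that the documents do not support:

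- **That the trial may succeed on either rating.** No such rule is printed. Step 3 shows only what would follow from one.
- **That pain, quality of life and movement are co-primary.** The aims sentence stands alone. The abstract, the outcome sections, the sample size and the analysis all work with one primary outcome. It is a wording conflict to reconcile, and a multiplicity figure for three or more outcomes should not be charged to the plan.
- **That the article breaks its own principle.** The Lequesne section says of that index: "There is no investigator bias, which always has to be recognised within procedures combining self-rating and rating by another person". This concerns procedures that combine the two kinds of rating. No text says the two pain records are combined. The remark supports general caution about investigator ratings and no more.
- **That the diary is free of bias.** The patient learns the allocation from the same envelope. The documents do not show that the investigator's score is the more biased of the two.

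**Conclusion.** The point holds as a defect of definition. As printed, the primary outcome is two records treated as one variable, without a deciding rule. One of them is an unblinded third party's rating of a subjective symptom, and the aims section contradicts the ranking of outcomes used elsewhere.

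The size depends on a rule that is not printed. The false-positive chance is about 7% to 10% if either rating may count, assuming alpha 0.05 each and correlations of 0.9 down to 0. There is no inflation if both must succeed. The amount of detection bias cannot be calculated from the documents. The lack of a defined answer when the ratings disagree depends on none of these assumptions. The matter should be settled before outcome data are examined.

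**What to change.** - In the abstract and under *Primary outcome measure*, name the patient-diary VAS over the inpatient stay as the single primary outcome.
- Keep the repeated-measures ANOVA already planned under *Statistical analysis*, and state there that the VAS is the patient's diary rating. A new summary measure is not needed and would change the endpoint.
- Move the investigator's VAS to the secondary outcomes.
- Reword *Research aims and questions* so that pain is the main outcome, with quality of life and movement secondary.

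**Cost.** The change adds no test and no data collection, and the 180 patients need not change. The sponsor gives up the investigator's rating as a primary result.

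**What remains.** The change removes the ambiguity and keeps the investigator's rater bias out of the primary outcome. It does not remove the expectation bias of patients who know their treatment, and the report should say so.

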### Secondary outcome measures

#### I) Mobility of the affected joint

The mobility of the affected hip or knee joint is documented by the investigator at the time of admission and the time of discharge from the clinic, using the neutral-zero method and range of motion scale. Flexion and extension, internal and external rotation are recorded for the hip joint, as are flexion and extension for the knee joint.

#### II) Quality of life rating for the patient with osteoarthritis, on the basis of the German version of the Arthritis Impact Measurement Scale (AIMS2)

The practicality, reliability and validity of the Arthritis Impact Measurement Scale (AIMS2) have been confirmed in many studies, and for this reason it is used in judging the quality of life in patients with osteoarthritis. Its inherent consistency and reliability are similar to those of the WOMAC score, with Cronbach's alpha at 0.77 or higher [32]. The patient will document this index at the beginning and end of the inhouse treatment period, and it will again be recorded by the external evaluation centre on the basis of the telephone interview at the end of the ten-week follow-up.

#### III) Joint-specific pain and function rating on the basis of the Lequesne index

The Lequesne index is a patient-centred assessment (self-rating procedure) in the form of a questionnaire. It is available in two closely related versions (hip or knee joint diseases), and includes pain, walking performance, and coping with daily living. The evaluation shows high reliability, validity, and sensitivity to change.

As a self-rating procedure, the Lequesne index is not subject to the influence of the investigator or therapist. There is no investigator bias, which always has to be recognised within procedures combining self-rating and rating by another person. The Lequesne index is therefore a suitable assessment tool for quality assurance [33,34]. The patient will document this index for the affected joint at the beginning and end of the inhouse treatment period, and it will again be recorded by the external evaluation centre on the basis of the telephone interview at the end of the ten-week follow-up.

#### IV) Rating the general health-related quality of life on the basis of the SF-36, short version

The SF-36 is an internationally recognised tool for ascertaining patients' health-related quality of life in a wide range of diseases. It comprises two summation scales and eight dimensions, which can be divided into the areas of "physical health" and "mental health". The inherent consistency (Cronbach's alpha) for "physical function" is between 0.77 and 0.93, between 0.73 and 0.85 for "pain", and between 0.57 and 0.75 for "general health perception". Its validity and reliability have likewise been evaluated scientifically [35,36]. The short version of the SF-36 that we use will be recorded by the patient at the beginning and the end of the inhouse treatment period and again by telephone by the external evaluation centre at the end of the ten week follow-up.

#### V) Rating the indirect flexion and extension ability of the hip or knee joint and general patient mobility through the timed "up and go" (TUG) test

In its original form, the TUG is an internationally recognised procedure for rating body balance and the danger of falling during an everyday task involving movement. For this reason, it is a standard procedure in geriatric and general practitioner assessment of individual patient mobility and risk of falling. The TUG's validity, inherent consistency, and reliability are scientifically proved [37]. To carry out the test, the patient sits on a chair with armrests, which is placed three metres from a wall. When prompted, the patient has to stand up, pause in front of the chair, walk the three metres to the wall, turn around without touching the wall, walk back to the chair, turn around again and sit down. The time required, use of aids, and general feasibility are measured. We use the TUG test, together with an estimate of general mobility, to rate flexion and extension of the affected knee or hip joint indirectly, as described previously in the scientific literature for the indication of osteoarthritis [38]. The TUG test will be administered by the investigator at the beginning of the study and again at the end of the inpatient treatment phase

#### VI) Standardised survey of state of health based on the EQ-5D test

The EQ-5D test is a standardised international procedure for self-rating of the patient's health status. It is divided into a general descriptive part and a pain-related part. The five dimensions rated in the descriptive part are mobility, self-sufficiency, daily activities, pain or discomfort, and anxiety or depression; the pain section of the EQ-5D test consists of the visual analogue scale in the self-rating procedure. In contrast to the SF 36 and the AIMS2, a more exact rating of everyday activities and their disease-related restriction is possible. The inherent consistency and validity of the EQ-5D test have been well evaluated scientifically [39].

In the EQ-5D self-rating procedure, results will be recorded by the patients at the beginning of the study and at the end of the treatment phase; the external study evaluation centre will also collect data by telephone ten weeks later.

#### VII) Blood pressure profile during the inpatient treatment phase

To demonstrate possible concomitant effects of the inpatient therapy on blood pressure – especially in the hydrotherapy group and the group combining hydrotherapy with physiotherapy – nursing staff will record the patient's blood pressure each day in the patient's diary.

#### VIII) Body weight changes during the inpatient phase, based on the BMI

The investigator will record the patient's BMI at the beginning of the study and at the end of the inpatient treatment phase.

### Statistical analysis

The data will be analysed using SPSS 15.0 (SPSS inc., 2006) software according to the intention-to-treat principle. Accordingly, all patients with valid values will be included in such a way that they remain in the groups in which they were originally randomised, irrespective of the treatment they actually received.

To check the homogeneity of the groups, a cross-sectional comparison of the baseline characteristics will be carried out. Various statistical procedures will be applied, depending on the scale level in each case. A factorial analysis of variance (one way ANOVA), if necessary with appropriate post hoc tests, will be carried out for the metric variables, body mass index (BMI), age and blood pressure, the scale values in SF-36, AIMS 2-F, visual analogue scale (VAS), and Lequesne index, the time required in the timed "up and go" test, and flexion and extension in the neutral-zero testing,. The nominal variables sex, affected joint (left, right, both sides) and the items of the EQ-5D will be analysed with chi-square tests. An analysis of variance with measured value repetition (ANOVA, repeated measures) will be performed for the longitudinal analysis of the primary outcome measure (VAS), and for the secondary outcome criteria (current mental health state, SF-36 sum scales, AIMS 2-SF scales, Lequesne index, time required in the timed "up and go" test, flexion and extension in the neutral-zero testing, and blood pressure) which are also metric variables. Should, contrary to expectations, there be any inhomogeneity between the groups with respect to important variables (baseline characteristics), adjustments will be made as far as possible in the scope of the longitudinal analysis. The secondary outcome measures on the nominal data level (EQ-5D) will be analysed with chi-square tests.

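### Hip versus knee is missing from the listed baseline comparison and longitudinal models, and hip rotation is collected but not listed for analysis

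*Protocol article*

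**What the plan says.** All places are in the protocol article.

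- **Population.** The abstract states: "One hundred and eighty patients diagnosed with osteoarthritis of hip or knee will be randomly assigned to one of three intervention groups". Table 1 admits either joint under one inclusion criterion.
- **Baseline comparison.** Statistical analysis names its variables one by one. For joints it says: "The nominal variables sex, affected joint (left, right, both sides) and the items of the EQ-5D will be analysed with chi-square tests". Those categories are sides.
- **Mobility as collected.** Secondary outcome I: "Flexion and extension, internal and external rotation are recorded for the hip joint, as are flexion and extension for the knee joint". The section on the diagnostic and biometric evaluation procedure gives the same movements.
- **Mobility as analysed.** The longitudinal list ends with "flexion and extension in the neutral-zero testing, and blood pressure". The baseline list also has only flexion and extension.
- **Lequesne index.** Secondary outcome III says: "It is available in two closely related versions (hip or knee joint diseases". Statistical analysis enters the index once, without version or joint.
- **Adjustment.** If important baseline characteristics turn out inhomogeneous between groups, the longitudinal analysis is to be adjusted as far as possible.
- **Allocation.** The randomisation section describes a software-generated list and mentions no stratification by joint.

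**The concern.** Joint type determines which movements are measured, which Lequesne version is used and which joint the physiotherapy in groups 2 and 3 addresses. It is nevertheless absent from the lists of variables to be compared and modelled. Three things follow.

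1. If the arms differ by chance in their share of hip patients, the listed baseline check will not show it, so the conditional adjustment will not be triggered.
2. A single flexion variable taken across all patients combines degrees at the hip with degrees at the knee. An arm difference in that average is hard to interpret for either joint.
3. Hip rotation belongs to a declared secondary outcome, but no analysis is listed for it.

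Movement in the affected joint is not a marginal outcome. The research aims place it among the main outcome measures, beside pain and quality of life.

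**Working it through.** **The plan's own figure.** The Sample size section says that "a sample size of n = 180 patients will suffice to determine a possible interaction between the groups with respect to the primary outcome", at 95% power. Alpha, effect size, correlation and number of measurements are not given in the article, so 180 can be neither reproduced nor refuted. Back-solving with the noncentral F for a group-by-time interaction (3 groups, assumed alpha 0.05, 2 measurements, assumed correlation 0.5) gives f = 0.148, which is a plausible input. The present point does not depend on it.

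**Text check: collected against listed.**

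| Item | Collected or defined | Baseline list | Longitudinal list |
|---|---|---|---|
| Hip versus knee | Eligibility; decides movements and Lequesne version | Not listed (side only) | Not listed |
| Flexion, extension | Separately for hip and knee | One entry | One entry |
| Hip internal and external rotation | Secondary outcome I | Not listed | Not listed |
| Lequesne index | Hip version and knee version | One entry | One entry |
| BMI | Secondary outcome VIII | Listed | Not listed |

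The BMI row shows that the longitudinal list is not exhaustive. Rotation differs in that it is missing from both lists, while flexion and extension from the same examination are in both.

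**How large a chance imbalance could go unseen.** Assumptions: equal arms of 180/3 = 60 (the ratio is not stated), no stratification, hip share p between 0.3 and 0.5 (not stated).

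95% bound on the difference in hip share between two arms = 1.96 × sqrt(2p(1 − p)/60):

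- p = 0.3: 1.96 × sqrt(0.42/60) = 0.164
- p = 0.5: 1.96 × sqrt(0.50/60) = 0.179

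Across all three arms, simulation under the same assumptions gives a largest gap of 15 points or more in about 21% to 27% of randomisations, and of 20 points or more in about 6% to 9%.

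**Illustrative effect on a range-of-motion comparison.** Shift in the arm difference = gap in hip share × difference between joints in mean change. With an assumed 10-degree difference in change:

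- 0.164 × 10 = 1.6 degrees
- 0.179 × 10 = 1.8 degrees

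The shift is proportional to the assumed difference: 5 degrees would give 0.8 to 0.9, and none would give zero. The article supplies no figure for it.

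**Cost of separate analyses.** For an assumed standardised difference of 0.5 between two arms, two-sided 0.05:

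| Analysis | Patients per arm | Power |
|---|---|---|
| All patients | 60 | 0.78 |
| Each joint, 50/50 split | 30 | 0.49 |
| Knee, 70/30 split | 42 | 0.63 |
| Hip, 70/30 split | 18 | 0.32 |

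**The case against.** The strongest reply is that this is a condensed article. No sentence says that hip and knee degrees will be averaged, and the outcome section already defines the movements by joint, so the single entry for flexion and extension could be shorthand for joint-wise analysis. It is true that pooling is an inference from the lists. But those lists are explicit, they define the affected joint by side, and they leave rotation out twice. Clarification is needed whichever reading was meant.

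Second, randomisation balances joint type in expectation, and chance imbalance is already covered by the error rate of the test. That stands: the plan is not biased by omitting joint type. What is lost is precision, where joint type predicts change, and the ability to see an imbalance.

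Third, adjustment for inhomogeneous baseline variables is already promised, and joint type must be known to choose the Lequesne version. Adjustment therefore remains possible. It is not assured, because the check that would trigger it does not list hip/knee.

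A reader might go further and infer the following, which the article does not support:

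- **That the two Lequesne versions are different scales.** The article calls them closely related and gives no scoring. The secure statement is that two versions are entered as one variable.
- **That hip rotation will never be analysed.** The longitudinal list also omits BMI, so absence shows only that rotation is not listed.
- **That mixing joints inflates the variance of the treatment test.** A constant hip-knee difference in level largely drops out of within-patient change and hence of a group-by-time test. It widens the cross-sectional baseline spread. Only a joint difference in change affects the longitudinal comparison.

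**Conclusion.** The point holds as a defect in the variables that the plan lists. Hip versus knee is in neither the baseline comparison nor the repeated-measures models, flexion and extension are undifferentiated by joint, and hip rotation is unlisted although it is part of secondary outcome I. The consequence is limited to interpretability and precision of the joint-specific secondary outcomes, and to chance imbalance that the planned check would miss.

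The text check needs no assumptions. The 1.6 to 1.8 degrees is illustrative only: it rests on 60 per arm, a hip share of 30% to 50% and a 10-degree difference in change, none of them stated in the article, and it is a 95% bound, not an expected error.

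Two wider conclusions do not follow. The primary outcome has no scale problem, because pain is rated on the same visual analogue scale for both joints; including joint type in that model is good practice and not needed for validity. Nor does the article show that the measured joint in bilateral patients would be picked after the arm is known. It states no index-joint rule, but such a rule is commonly left to the full protocol or case report form. Stating one would be sensible, and this finding does not depend on it.

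**What to change.** 1. Add hip/knee to the baseline comparison and show it by arm, alongside side.
2. Include joint type as a factor in the primary and secondary longitudinal models, fixed in advance and not conditional on observed imbalance. Where the treatment test is the group-by-time term, include the joint-by-time term as well; otherwise the adjustment does not reach that test.
3. Analyse neutral-zero range of motion separately: flexion, extension, internal and external rotation for the hip; flexion and extension for the knee. This also brings the analysis lists into line with secondary outcome I.
4. Model the Lequesne index with joint type as a factor.

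No extra patients, visits or measurements are needed, since joint type must already be known at the admission assessment. The cost is a few lines of analysis wording and lower precision for each joint's range of motion: on the assumptions above, power of 0.32 to 0.63 per joint against 0.78 for all patients together. The per-joint results should therefore be presented with confidence intervals and read as secondary.
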